**Methods/design:**

Multicentre randomized, controlled clinical trial. Location: Primary health care centres in the city of Tarragona and surrounding areas. Subjects: 70 primary care patients, aged 18 years or older, with body mass index of 25 g/m2 or greater who wish to lose weight. Description of the intervention: 12 months of standard diet recommendations without (*n* = 35) or with (*n* = 35) assistance of a free Smartphone app that allows the participant to maintain a record of dietary intake and a bracelet monitor that records physical activity. The outcomes will be weight loss at 12 months (primary outcome), changes in physical activity and cardiometabolic risk factors, frequency of app use, and participant satisfaction after 12 months.

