### Sample size

Accepting an alpha risk of 0.05 and a beta risk of 0.2 in a two-sided test, **70** subjects are necessary in each group, with an estimated 30 % loss to follow-up, to recognize as statistically significant a difference greater than or equal to 3.9 kg [22]. The common standard deviation is assumed to be 4.826 kg.

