### Statistical analysis

Analysis will be based on intention to treat. Basal analysis will determine the comparability of the two study groups according to the study variables. Quantitative variables with a normal distribution will be described as means and standard deviation, or median and interquartile range otherwise, and qualitative variables as percentages and 95 % confidence intervals. Quantitative basal characteristics will be compared using Student *t* test and qualitative variables using Pearson chi-square test.

A hierarchical linear model (HLM) will be used for longitudinal data, presented as a 2-level hierarchical structure: level-1 units consist of the repeated measures for each subject, and level-2 units will be the subject. HLM allows the estimation of inter-individual differences in intra-individual change over time by modelling the variances and co-variances. All covariables that are significant at *p* < 0.30 in bivariate analysis will be included in the model. This strategy will sufficiently reduce the probability of leaving relevant variables out of the model.

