## Discussion

One of the study limitations is its open design. It is impossible to mask the intervention; both patients and health professionals in the experimental and control groups will be aware that they are participating in a weight loss intervention, which could affect the success or failure of the intervention and has the potential to introduce bias. Randomization of patients to study groups will help to achieve a balance in sociodemographic and anthropometric characteristics, as well as risk factor profile. Potential confounding factors will be controlled by applying the appropriate multivariate analysis. The researcher responsible for the statistical analysis will be blinded to study group assignments.

Although the study results cannot be applied to all health-related mobile apps, limiting the external validity of the study, they will likely be generalizable to apps with characteristics similar to this free app. Another possible limitation is the length of the study period. One of the great challenges to patients who have lost weight is to maintain the weight loss longer than a year. Based on the study results, however, follow-up strategies will be designed to support participants beyond the end of the study period within the framework of the universal primary care system in Catalonia.

Among the strengths of the study is that this clinical trial has the potential to provide a validated weight loss tool that could be very useful to patients accessing primary health care who want to lose weight. Very few studies to date have validated the effectiveness of weight loss apps, and none of them were done in our setting.

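### The p < 0.30 covariate screen leaves the primary model to the data; depending on how it is applied it attenuates the effect, costs power or gains nothing, and a short list named in advance would do better

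*Protocol article*

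**What the plan says.** The Statistical analysis section specifies a two-level hierarchical linear model, with repeated measures nested in subjects, analysed by intention to treat. Its covariates are all those with p "< 0.30 in bivariate analysis will be included in the model", and the reason given is to avoid omitting relevant variables. The same section says "Basal analysis will determine the comparability of the two study groups according to the study variables", using t and chi-square tests. The Discussion adds: "Potential confounding factors will be controlled by applying the appropriate multivariate analysis".

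Three things are left open: whether the bivariate test is against weight change or against group, which variables are candidates, and whether baseline weight is a repeated measure, a covariate or part of a change score. The Data collection section lists well over ten baseline variables: sociodemographics, toxic habits, medication, blood tests, waist, blood pressure, diet and physical activity.

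**The concern.** Randomisation already removes systematic confounding, so the reason to adjust is precision. That is best obtained by naming a few strong baseline predictors beforehand, of which baseline weight is the obvious one. A screen at 0.30 admits about three in ten pure-noise variables and does not guarantee that baseline weight is kept when it is treated as a covariate.

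A screen against the outcome that ignores group also interacts with the treatment effect. Take a standardised noise covariate with chance group imbalance d and within-group slope b on weight change, and let D be the observed group difference. Under 1:1 allocation the pooled slope is about b + D·d/4, and adjustment changes the estimate from D to about D − b·d. The screen favours covariates for which b and D·d have the same sign, and those are the ones for which subtracting b·d moves the estimate towards zero. At stake are the size of the reported effect and the power of a small trial.

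**Working it through.** **Inputs from the Sample size section.** "Accepting an alpha risk of 0.05 and a beta risk of 0.2 in a two-sided test"; "a difference greater than or equal to 3.9 kg"; "The common standard deviation is assumed to be 4.826 kg"; 30 % loss.

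**The plan's own figure.** n per group = 2 × (1.960 + 0.842)² × 4.826² / 3.9² = 24.04. Allowing for loss, 24.04 / 0.7 = 34.3, so 35 per group and 70 in total, as in the abstract ("Subjects: 70 primary care patients, aged 18 years or older"). The Sample size section instead prints 70 as the number of which it says "subjects are necessary in each group, with an estimated 30 % loss to follow-up"; its inputs do not reproduce that. With 70 in total, 70 × 0.7 = 49 remain; with 70 per group, 140 × 0.7 = 98.

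**Assumptions not in the documents.** The number of candidates (5, 10 or 20, independent) and their joint R² with weight change (0, 0.2 or 0.4, from 0 to 3 prognostic variables).

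**Reading A: screen against weight change, covariates adjust the 12-month change.** Linear model, true effect 3.9 kg, SD 4.826, 49 analysed, 2,500 simulated trials per row. The pre-specified set is exactly the prognostic variables; at R² 0 it is empty.

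| Candidates | R² | Mean estimate under the rule (kg) | Power: no adjustment | Power: pre-specified | Power: rule |
|---|---|---|---|---|---|
| 5 | 0 | 3.74 | 79.8 % | 79.8 % | 75.6 % |
| 5 | 0.2 | 3.78 | 78.3 % | 86.9 % | 84.7 % |
| 10 | 0 | 3.57 | 78.5 % | 78.5 % | 71.8 % |
| 10 | 0.2 | 3.64 | 79.5 % | 85.7 % | 80.4 % |
| 10 | 0.4 | 3.72 | 77.9 % | 93.9 % | 90.4 % |
| 20 | 0 | 3.33 | 78.6 % | 78.6 % | 65.1 % |
| 20 | 0.2 | 3.41 | 79.0 % | 85.8 % | 72.4 % |
| 20 | 0.4 | 3.51 | 79.2 % | 93.3 % | 85.4 % |

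- Attenuation runs from (3.9 − 3.78)/3.9 = 3 % to (3.9 − 3.33)/3.9 = 15 %. The pre-specified set gave 3.89 to 3.93 kg throughout.
- The power deficit against the pre-specified set runs from 86.9 − 84.7 = 2.2 to 78.6 − 65.1 = 13.5 points.
- A run of 4,000 trials per setting with 10 and 20 candidates agreed within 3 points of power and 0.03 kg. Type I error stayed at about 5 %.
- With baseline weight as the only prognostic candidate (assumed correlation 0.3 with weight change), 10 / 20 candidates gave 3.63 / 3.38 kg and 76 / 69 % power. Baseline weight alone gave an unbiased estimate and 82 %. The screen dropped baseline weight in about 17 % of trials.
- With 98 analysed, 10 or 20 candidates gave 3.58 to 3.84 kg and a power loss of 0 to 3 points.

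**Reading B: screen against group.** Under randomisation any baseline variable passes with probability 0.30, so baseline weight is left out in about 70 % of trials. With 49 analysed the mean estimate was 3.86 to 3.93 kg (no attenuation). Power was 66 to 80 %, against 79 to 93 % for the pre-specified set; with 20 mostly noise candidates it was about 67 %, against 82 % for baseline weight alone. Type I error was 3.0 to 4.7 %.

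**Reading C: repeated-measures model.** With weight at 0, 3, 6 and 12 months, random intercept and slope, complete data and selected covariates as main effects only (1,500 trials per setting), the group-by-time result was the same with and without them: 3.91 against 3.91 kg and 80.4 % against 80.4 % with 10 candidates; 3.89 against 3.89 kg and 79.4 % against 79.4 % with 20. This is expected: a covariate that is constant over time and not crossed with time shifts a subject's level, not the within-subject change. If change scores are the repeated response, the main effects do act on the contrast, and a smaller attenuation appeared (3.78 against 3.92 kg, power 78 % against 82 %).

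**The case against.** The strongest objection is that the planned analysis is a hierarchical model of change over time, not a regression of 12-month change. Under Reading C the bias is absent, and baseline weight, as a level-1 observation, cannot be screened out. This stands: a reader might infer that the primary estimate will be biased toward zero, and the article does not support that without knowing the model form. The sentences before the rule compare the groups at baseline, so a group screen is also possible, and it brings no attenuation.

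Nor is it general that the planned power is lost. With R² 0.2 and 10 candidates the rule still gives about 80 %, and with R² 0.4 it beats no adjustment (85 to 90 % against 78 to 79 %). A mixed model need not drop incomplete participants; with 70 analysed, outcome screening over 10 to 25 candidates gave 91 to 85 % power, against 93 % with baseline weight pre-specified. The comparator in the table is also favourable, because it assumes that the named covariates are the prognostic ones.

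Two further inferences are unsupported. The wording does not restrict candidates to variables measured before randomisation, but nothing says that follow-up activity or intake would be entered. There is also no sign of more false positives: the rule is stated in advance, the analyst is blinded, and type I error was not inflated.

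What remains is that no reading examined shows an advantage for the rule over a sensible list fixed beforehand, and two of the three show a cost.

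**Conclusion.** The point holds in conditional form. The primary model's covariates are left to a data-driven screen and none is fixed. With outcome screening that adjusts the change contrast, attenuation is roughly 3 to 15 % and power is about 2 to 14 points below a pre-specified set, at 49 analysed with 5 to 20 candidates. With group screening there is no attenuation, but power falls and baseline weight is usually omitted. With baseline weight at level 1 and covariates as main effects only, there is essentially no effect and no gain.

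These sizes rest on assumed numbers and strengths of candidates, on independence between them, and on 70 participants in total; at 98 analysed they are much smaller. This should be fixed, but it does not by itself invalidate the trial.

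**What to change.** Delete the p < 0.30 sentence and the justification that follows it. Name the primary model in advance: group, visit, group-by-visit and baseline weight, optionally with centre, age and sex, using only variables measured before randomisation. State whether baseline weight enters as a covariate or as a repeated measure. Present baseline characteristics descriptively and do not let baseline tests choose covariates. Label any data-selected model a sensitivity analysis. The cost is two sentences of analysis text and no new data. Reconciling 70 in total with 70 in each group would also settle which of the sizes above applies.

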### Ethical aspects of the study

The study will be conducted in accordance with the principles of the Helsinki Declaration, as revised and updated, and will follow Spain’s best practice guidelines (*Buena Práctica Clínica*). The protocol and all pertinent documents have been evaluated and approved by our institute’s ethics committee (*Comité Étic de Investigació Clínica [CEIC], Institut d’Investigació en Atenció Primària [IDIAP] Jordi Gol*). Data confidentiality will be protected under the Spanish law governing the protection of personal data (Ley orgánica de Protección de Datos de Carácter Personal (15/1999 13 December).

## Discussion

One of the study limitations is its open design. It is impossible to mask the intervention; both patients and health professionals in the experimental and control groups will be aware that they are participating in a weight loss intervention, which could affect the success or failure of the intervention and has the potential to introduce bias. Randomization of patients to study groups will help to achieve a balance in sociodemographic and anthropometric characteristics, as well as risk factor profile. Potential confounding factors will be controlled by applying the appropriate multivariate analysis. The researcher responsible for the statistical analysis will be blinded to study group assignments.

Although the study results cannot be applied to all health-related mobile apps, limiting the external validity of the study, they will likely be generalizable to apps with characteristics similar to this free app. Another possible limitation is the length of the study period. One of the great challenges to patients who have lost weight is to maintain the weight loss longer than a year. Based on the study results, however, follow-up strategies will be designed to support participants beyond the end of the study period within the framework of the universal primary care system in Catalonia.

Among the strengths of the study is that this clinical trial has the potential to provide a validated weight loss tool that could be very useful to patients accessing primary health care who want to lose weight. Very few studies to date have validated the effectiveness of weight loss apps, and none of them were done in our setting.
